## 1.1 Background

The global prevalence of diabetes has nearly doubled, from 4.7% in 1980 to 8.5% in 2014. Worldwide, approximately 463 million adults are living with diabetes mellitus (International Diabetes Federation [IDF], 2019) and most of them are type 2 diabetes mellitus (T2DM)(World Health Organization [WHO], 2019). Diabetes mellitus is increasing more rapidly in low-and middle-income countries than in high-income countries. South-East Asia and Western Pacific Regions have the largest number of people with diabetes mellitus, accounting for approximately half of the diabetes mellitus cases worldwide. An estimated 1.6 million deaths in 2015 were directly caused by diabetes mellitus (WHO, 2016) and it was estimated that the annual global health care spending on diabetes was US$ 850 billion in 2017 (IDF, 2017). It is a significant challenge for healthcare systems with such a high cost (IDF, 2015).

In Malaysia, diabetes mellitus is also a public health concern. The prevalence of diabetes mellitus among adults of 18 years and above has increased from 11.6% in 2006 to 17.5% in 2015 (Letchuman et al., 2010; Institute for Public Health [IPH], 2015) and is projected to be 21.6% by the year 2020 (Feisul and Azmi, 2013). There has also been an increasing prevalence of T2DM among adults aged ≥ 30 years in Malaysia, affecting 2.8 million individuals (Zanariah et al., 2015). The Indians had the highest prevalence of diabetes mellitus at 22.1%, followed by the Malays (14.6%) and Chinese (12.0%)(IPH, 2015). Diabetes mellitus has also been listed as one of the top 10 causes of premature mortality in Malaysia (Ummi et al., 2013).

T2DM is characterized by chronic hyperglycemia or high level of glucose in blood which stem from increased insulin resistance and insufficient levels of insulin (Olokoba, Obateru & Olokoba, 2012). People with long term hyperglycemic and insulin resistance will have increased risk of macrovasular and microvascular complications (IDF, 2015) and higher mortality (Holman, 2012). Complications of diabetes mellitus will adversely affect quality of life (Gupta, 2008) and reduce life span (Department of Health, 2012; Olivia et al., 2012; Podbielska et al., 2013; Cisneros et al., 2015).

Epidemiological experimental and clinical trials indicated that physical inactivity and some dietary practices are strongly associated with T2DM (Goedecke and Ojuka, 2014). It is estimated that more than 90% of diabetes mellitus cases could be prevented by engaging in moderate to vigorous physical activity for at least a half an hour per day, maintaining good nutrition, weight control, and smoking cessation (Morewitz, 2006). It is also demonstrated that physical activity may contribute to 30–50% reduction in the development of T2DM (Bassuk and Manson, 2005). Despite the importance of physical activity in the prevention of diabetes mellitus, physical inactivity remains the key reason for causing approximately 27% of diabetes mellitus cases in the world (WHO, 2013).

When lifestyle approach fails to maintain adequate glycemic control, pharmacological agents in the forms of oral, inhaled and injectable products are used to manage T2D (Charles, 1998; Ibrahim, 2010; Currie, 2012). However, these medications have limitations related to patient’s poor adherence (Currie et al., 2012; Gelaw et al., 2014; Reach, 2015; Kassahun et al., 2016), patient resistance to intensify treatment and doctors’ clinical inertia (Grant et al., 2011; Currie et al., 2012; Reach, 2015; Khunti et al., 2015). These limitations may be associated with the fear of side-effects of diabetes mellitus medication (Ruzaidi et al., 2008; Zafar et al., 2010; Khunti, 2015; Kassahun et al., 2016). Complementary and alternative medicine (CAM) may provide a beneficial adjunctive therapy for diabetes mellitus due to its perceived less adverse effect and culturally more acceptable in Asian population. Among the CAM, acupuncture is one of the most widely used combined therapies with conventional treatment for T2DM (Lin et al., 2013; Lin et al., 2014; Tjipto, 2014; Firouzjaei et al., 2016; Dong et al, 2017).

Acupuncture is a technique involving the insertion of fine needles into specific points on the body surface (British Acupuncture Council, 2019). It has been used for more than 2,500 years since its inception in China (VanderPloeg & Yi, 2009). It is an integral part of traditional Chinese medicine (TCM) or traditional medicine (TM). TM has a long history of use in health maintenance and in disease prevention and treatment, particularly for chronic disease (WHO, 2013). According to the theory of TCM, acupuncture can regulate *qi* and *blood* and have a direct impact on bioavailability of substances of the body (Firouzjaei et al., 2016). Acupuncture has become more established in conventional treatment as an alternative or complement medicine (Elisabet, 2008; Takahashi, 2009).

Acupuncture has been shown to be effective in treating diabetes mellitus in clinical randomized controlled trials (RCTs)(Yang and Liu, 2015; Firouzjaei et al., 2016). According to Tjipto, Saputra & Sutrisno (2014), acupuncture as adjunctive therapy on diabetes mellitus showed significant decreased in fasting plasma glucose (FPG)(P<0.01) and oral glucose tolerances test (OGTT)(P<0.001). Similarly, it had been demonstrated that acupuncture combined with metformin was more effective than metformin alone on homeostasis model assessment-insulin resistance (HOMA-IR)(Firouzjaei et al. 2016)(weight mean difference (WMD) -1.34, 95%CI -1.56, -1.12, P<0.001), which acting as an insulin sensitizer improving insulin sensitivity (Liang and Koya, 2010; Lin et al., 2013) and c-peptide levels through effective treatment against metabolic disturbances such as hyperglycemia (Peplow and David, 2012; Tjipto, Saputra & Sutrisno, 2014), inducing weight loss (Cho et al., 2009; Tur et al., 2014; Firouzjaei et al., 2016) owing to its beneficial influence on hormones such as insulin, cholecystokinin, ghrelin and leptin (Zhang, et al. (2018), improving lipid metabolism (Liang and Koya, 2010; Lin et al., 2013; Firouzjaei et al., 2016) while capable of reducing inflammation (Wei et al., 2015). Additionally, acupuncture is able to control co-morbidity conditions such as anxiety (Frisk et al., 2012; David et al., 2013), depression (David et al., 2013), pain (Manyanga et al., 2014; Helianthi et al., 2016), stress (Mishra et al., 2017), sleeping disorder (Cao et al., 2009; Dong et al., 2017) and hence improved quality of life (Frisk, 2012; Vinjamury, 2013; Xiong et al., 2016).

The United States National Institutes of Health (NIH) has also acknowledged that acupuncture can be used as adjunctive treatment for diabetes (Takahashi, 2009). Equally, systematic reviews have also affirmed positive results of acupuncture as a complementary therapy for T2DM (Cai and Peng, 2010; Chen et al., 2019), diabetes complications (Yang, 2013; Lin et al., 2013; [name], 2013; Liu, 2016; Xiong, 2016) and obesity (Cho et al., 2009; Zhang et al., 2017; Zhong et al., 2020). Study showed that acupuncture was more effective than mecobalamin (RR 1.31, 95%CI 1.21-1.42), vitamin B1 and B12 (RR 1.55, 95% CI 1.33-1.80), and no treatment (RR 1.56, 95% CI 1.31-1.85) on global neuropathic symptoms (Chen et al., 2013). Additionally, acupuncture was highly effective in decreasing body mass index (BMI)(MD=-1.22, 95%CI=-1.87 to -0.56; P<0.001) and body weight (MD=-1.54, 95% CI=-2.98 to -0.11; P<0.001) when compared to sham acupuncture in reducing obesity (Zhang, et al. 2018). However, multiple methodological flaws with substantial risk of bias have been identified in many of these RCTs (Bo et al., 2012; Yang, 2013; Xiong et al., 2016; Dimitrova et al., 2017; Zhong et al., 2020).

Safety is one of the most important issues in the use of acupuncture in clinical practice, especially for diabetes mellitus. According to various prospective studies in China, Korea, Japan, Germany and the United Kingdom, serious adverse event associated with acupuncture is rare (Park et al., 2010; Witt et al., 2011; He et al., 2012; Birch, 2013) where the incidence rate was about 0.004%. Moreover, systematic reviews on acupuncture published between January 2005 until March 2013 found that adverse events were not significant and suggested for more standardized procedures including adverse events reporting mechanisms, safe practice procedures, acupuncturist’s qualifications and training (Hempel, Taylor, Solloway et al., 2013). Nevertheless, as compared with medications routinely prescribed in primary care, acupuncture is a relatively safe treatment modality with minimum side effects if it is performed properly by a well-trained practitioner (MacPherson et al., 2008).

Acupuncture is a new treatment modality, emerging within the last two decades. Currently, there are limited well-designed RCTs to determine the efficacy of acupuncture on diabetes mellitus. The purpose of this study is to conduct a clinical trial to assess the effect of acupuncture as adjunctive therapy in patients with T2DM in accordance with the consolidated Standards for Reporting of Trials Statement 2010 (CONSORT 2010)(Schulz Altman & Moher, 2010) and revised Standards for Reporting Interventions Controlled Trials of Acupuncture 2010 (STRICTA 2010)( MacPherson et. al., 2010) guidelines.

## 1. 2 Objectives:

### 1.2.1 General objective:

To determine the effect of acupuncture treatments on Homeostasis model assessment-insulin resistance (HOMA-IR) and health-related quality of life (HRQoL) in patients with T2DM***.***

### 1.2.2 Specific Objectives:

1. To compare
2. Socio-demographic background (age, gender, ethnicity, marital status, levels of education, employment, personal income);
3. Clinical characteristics (duration of disease, glycemic control, family history of disease)
4. Physical examinations (body weight, body mass index (BMI) and waist circumference (WC)

between acupuncture and control groups at baseline.

1. To examine the effect of acupuncture towards change in the HOMA-IR and/or HRQoL within and between acupuncture and control groups after treatment.
2. To identify the presence of adverse event in patients with T2DM between acupuncture and control groups.

## 1.3 Hypothesis:

There is significant effect of acupuncture towards change in the HOMA-IR and/or HRQoL within and between acupuncture and control groups after treatment.

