## 1.4 Research Framework

This study intended to investigate the effect of acupuncture treatments on HOMA-IR and HRQoL of T2DM patients in Malaysia context. The effectiveness of the intervention will be examined through the change in HOMA-IR and/or HRQoL within and between the acupuncture and control groups after treatment. Consequently, the safety of acupuncture treatment will be identified between the acupuncture and control groups. A total of 10 sessions of acupuncture or placebo treatment will be provided to the intervention and control groups. Both groups will continue with their routine diabetes care. The primary outcome is the change of HOMA-IR while the secondary outcome is the change in HRQoL among two intervention groups. Figure 1 shows the treatments and variables to be investigated in this study.

**
[figure not shown]
**

**Figure1:** Research Framework

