## 2.4 Sample Size

The sample size calculation is based on previous study (Firouzjaei et al. 2016) where the mean differences of HOMA-IR and standard deviation between two groups were 1.23 and 1.25 respectively. For the mean comparison method of two-sample t-test model, a significance level of 5% z_(1-∂/2)_ = 1.96 and a power of 90% z_(1-ß)_ = 1.28 will be utilized to calculate the required sample size.

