### 2.10.5 Health-related Quality of Life

###

Patient’s health-related quality of life will be assessed using a validated World Health Organization Quality of Life Assessment: Brief Version (WHOQOL-BREF)(The WHOQOL Group, 1998; Hasanah, 2003). It consists of 26 items which represent four domains of psychological, social relationship, environmental, physical health domains and two facets of overall quality of life and general health. The question scores of all 26 items ranged from 1 to 5.

WHOQOL-BREF has been found to be comparable to the WHOQOL-100 and other WHOQOL (The WHOQOL Group, 1998; Hasanah, 2003). It is able to discriminate between patients and healthy people in revealing characteristic impairment of certain illness, including diabetes (Hasanah, 2003). The English or Malay versions of this instrument have been validated in Malaysia (Hasanah, 2003; Chew, Mohd-Sidek & Sharif-Ghazali, 2015). The Cronbach’s alphas coefficient of the WHOQOL-BREF was found to be satisfactory, ranging from 0.66 to 0.84 (WHO, 1998; Hasanah, 2003; Chew, Mohd-Sidek & Sharif-Ghazali, 2015).

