# 5. Statistical Analysis

Data will be analyzed using SPSS Statistics 26.0 (IBM Corp., New York, USA). Data will be presented as mean ± SD for continuous parameters and percentage for categorical data. Kolmogoro-Smirnov tests for normality will be performed on each parameter before analysis. Comparisons of background and baseline continuous variables between intervention and control group will be examined using independent t-test, while for categorical variables the chi-square test will be used. Intention-to-treat analysis (ITT) will be performed, and all patients enrolled will be included in the analysis, irrespective of compliance. The missing data is imputed using last observation carried forward method. Paired t-test will be carried out in analyzing the statistical significance of mean pre-post change in the parameters. The changes between groups on two time-points (pre-post) will be conducted using analysis of covariance (ANCOVA) if covariates are present. A repeated measure ANCOVA is performed to compare changes between groups at baseline, week 3/4 (6^th^ visit) and week 7 of intervention while controlling for a confounding variable. Mc Nemar’s test is utilized for matched pair’s comparison. However, if data are not normally distributed, non-parametric tests are used. The significant level for all tests is set at p<0.05 (two-tailed).

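### The hypothesis accepts HOMA-IR and/or HRQoL, so an HRQoL result alone can confirm it, although HOMA-IR is the named primary outcome and the only one the trial is sized on

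*Protocol*

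**What the plan says.** The hypothesis in Section 1.3 reads "There is significant effect of acupuncture towards change in the HOMA-IR and/or HRQoL within and between acupuncture and control groups after treatment". The effect objective in Section 1.2.2 has the same construction, and Section 1.4 repeats it as the way the treatment will be judged: "The effectiveness of the intervention will be examined through the change in HOMA-IR and/or HRQoL within and between the acupuncture and control groups after treatment".

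Section 1.4 also sets a hierarchy: "The primary outcome is the change of HOMA-IR while the secondary outcome is the change in HRQoL among two intervention groups". Section 2.4 uses HOMA-IR alone for the sample size, taking from a previous study that the "mean differences of HOMA-IR and standard deviation between two groups were 1.23 and 1.25 respectively", with a two-sample t-test, 5% significance and 90% power.

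Section 2.10.5 describes the HRQoL instrument as "four domains of psychological, social relationship, environmental, physical health domains and two facets of overall quality of life and general health". No one of these scores is singled out as the HRQoL outcome.

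Section 5 plans tests within and between arms. Within: "Paired t-test will be carried out in analyzing the statistical significance of mean pre-post change in the parameters". Between: "The changes between groups on two time-points (pre-post) will be conducted using analysis of covariance (ANCOVA) if covariates are present". On the threshold it says "The significant level for all tests is set at p<0.05 (two-tailed".

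**The concern.** The 5% error rate and 90% power in Section 2.4 belong to one test, the between-group comparison of HOMA-IR. The hypothesis can be met without that test, because *and/or* lets HRQoL stand in for HOMA-IR. The trial could then be reported as confirming its hypothesis while its primary outcome showed no difference between acupuncture and placebo.

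A second ambiguity lies in *within and between*. If a pre-post change in the acupuncture arm counted by itself, the placebo arm would have no part in the conclusion. Such a change also contains placebo response, attention, time trend and regression to the mean. Some of this is plausible here. Entry requires fasting glucose of at least 7.0 mmol/L (Section 2.5), fasting glucose is a factor in HOMA-IR (Section 2.10.4), and both arms attend ten sessions with the points pressed (Sections 2.7 and 2.7.2).

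**Working it through.** **1. The plan's own figure.** Inputs from Section 2.4: difference 1.23, SD 1.25, z values 1.96 and 1.28.

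n = 2 × (1.96 + 1.28)² × 1.25² / 1.23² = 2 × 10.4976 × 1.5625 / 1.5129 = 21.7, so 22 per group. The figure reproduces, as a single between-group HOMA-IR test.

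**2. Error rate of the *and/or* wording, between-group tests only.** Each test is at 0.05 (Section 5) and there is no true difference. For k independent tests the chance of at least one false positive is 1 − 0.95^k.

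| What can meet the hypothesis | k | Independent tests | Correlation 0.5 (assumed) |
| --- | --- | --- | --- |
| HOMA-IR only | 1 | 5% | 5% |
| HOMA-IR or one HRQoL score | 2 | 9.75% | about 9% |
| HOMA-IR or any of four domains | 5 | 22.6% | about 18% |
| HOMA-IR or any of four domains and two facets | 7 | 30.2% | about 23% |

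For seven tests, assumed correlations of 0.3 and 0.7 give about 27% and 18%. The correlated figures come from simulation. The protocol gives no correlations.

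**3. If a within-arm change alone counted.** Suppose both arms improve equally, by d standard deviations of the change, with no specific acupuncture effect. The acupuncture-arm paired t-test then has n − 1 degrees of freedom and noncentrality d√n. For n = 30 and d = 0.5 this is 0.5 × √30 = 2.74.

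| Assumed d | n = 30 (all randomised) | n = 22 (before dropout inflation) |
| --- | --- | --- |
| 0.3 | 36% | 27% |
| 0.5 | 75% | 61% |

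The between-group HOMA-IR test stays at 5% throughout. The values of d are assumptions; the protocol gives none.

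**4. If *within and between* requires both on the same outcome.** Simulation with 22 or 30 per arm, common shifts of 0 to 0.8 SD and correlations of 0 to 0.5 gives about 3–9% for two outcomes (HOMA-IR and one HRQoL score) and about 7–21% for five (HOMA-IR and four domains).

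**The case against.** **The text has an anchor.** One primary outcome is named and powered, Section 5 plans a between-group ANCOVA, and Section 6 expects gains in HOMA-IR and HRQoL relative to control. No passage calls the hypothesis a decision rule. This stands as mitigation: the primary outcome is not missing. It does not remove the conflict, because Section 1.4 uses the same loose wording to say how effectiveness will be examined.

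**The within-arm route depends on one reading.** A reader might infer that a trial with no between-arm difference at all could confirm its hypothesis. The text does not establish that. *And/or* joins the two outcomes, but a plain *and* joins within and between, so the sentence can be read as requiring both. The figures in step 3 apply only on the looser reading. They also fall under the protocol's own last-observation rule if dropouts contribute zero change: with 8 to 10 of 30 carried forward from baseline, to about 24–27% at 0.3 SD and 56–61% at 0.5 SD.

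**The larger family-wise figures are upper ends.** A reader might take 30% as the trial's error rate. No passage says that all six HRQoL scores will be tested separately or count towards the hypothesis, and independence is unlikely for scores from one questionnaire. Adding 14 within-arm tests to the seven between-group tests would be weaker still, since seven of them sit in the placebo arm and cannot show an acupuncture effect.

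**Multiplicity among HRQoL scores can sit in the SAP.** Agreed; its absence here is not a fault. The hypothesis itself is protocol content.

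**Conclusion.** The point holds. The effect objective, the hypothesis and the effectiveness statement conflict with the protocol's own primary outcome and sample size. The conflict does not depend on how *within and between* is read: even if both are required, an HRQoL result meets the hypothesis with no randomised difference in HOMA-IR.

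The firmest size is 9.75% against a nominal 5%, for HOMA-IR or a single HRQoL score with independent between-group tests. The 22.6% and 30.2% figures are upper ends that need every score to count and tests to be independent. On the strict reading the rate with two outcomes is only about 3–9%, so inflation there is modest or absent unless several HRQoL scores count. Whether a within-arm change alone would suffice is left open by the text, and the 36–75% range is conditional on that reading and on the assumed shifts.

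This is a badly fixed success criterion in a trial that otherwise has a named and powered primary comparison. It matters because it decides what the trial may conclude, and it should be settled before unblinding.

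**What to change.** Restate the effect objective in Section 1.2.2, the hypothesis in Section 1.3 and the effectiveness sentence in Section 1.4 so that:

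- the single confirmatory hypothesis is the between-group difference in HOMA-IR change at week 7, tested at two-sided 0.05;
- HRQoL is a secondary outcome, compared between groups, and cannot by itself confirm the hypothesis;
- within-arm pre-post changes are descriptive and are not evidence of an acupuncture effect, with the paired t-test sentence in Section 5 marked accordingly.

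The choice of HRQoL scores and any multiplicity method for them can be left to the SAP.

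The change is to wording only. It keeps the confirmatory error rate at 5% and leaves the calculation at 22 per group before dropout. By comparison, keeping HOMA-IR and one HRQoL score as alternative routes at 0.025 each would require 26 per group for HOMA-IR. The one loss is that HRQoL alone can no longer support a positive claim, which the hierarchy in Section 1.4 already implies.

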## 1.4 Research Framework

This study intended to investigate the effect of acupuncture treatments on HOMA-IR and HRQoL of T2DM patients in Malaysia context. The effectiveness of the intervention will be examined through the change in HOMA-IR and/or HRQoL within and between the acupuncture and control groups after treatment. Consequently, the safety of acupuncture treatment will be identified between the acupuncture and control groups. A total of 10 sessions of acupuncture or placebo treatment will be provided to the intervention and control groups. Both groups will continue with their routine diabetes care. The primary outcome is the change of HOMA-IR while the secondary outcome is the change in HRQoL among two intervention groups. Figure 1 shows the treatments and variables to be investigated in this study.

**
[figure not shown]
**

**Figure1:** Research Framework

# 2. Methodology

## 2.1 Study Location

The study will be conducted at seven centres in Malaysia namely i) Hospital Pengajar Universiti Putra Malaysia (HPUPM), [name]; ii) University Malaya Medical Centre, [name]; iii) TCM Clinical Skills Training Centre, School of Traditional Chinese Medicine, Xiamen University Malaysia (XMUM), [name]; iv) Klinik Kesihatan Bukit Kuda, [name]; v) Klinik Kesihatan Bandar Botanik, [name]; vi) Pusat Kesihatan Universiti Putra Malaysia, [name] and vii) Setia Chinese Medical and Acupuncture Centre, [name]. Permission will be obtained from the respective hospitals/institutions before conducting the research. The first three centres are either public or private university teaching clinics, the fourth, fifth and sixth centres are public or university health clinics while the last centre is a private clinic. Among all the centres, the third and last centres are providing TCM medical services to the public. The involvement of XMUM in the study in relation to research assistance are a) use of TCM Clinical Skill Training Centre, School of Traditional Chinese Medicine as one of the study site; b) assign qualified and experienced volunteer acupuncturist(s) for the study and c) assist and coordinate the research at XMUM site.

